## **Study design**

The study is a multicentre randomized controlled open trial. The study design is reported in Figure 1.

Immigrants with type 2 diabetes registered at the Italian Regional Health Service or provided with STP code will be recruited.

Across the four recruiting centres, at least four different immigrant communities will be involved.

Endocrinology and Diabetology physicians at Diabetes clinics of both the National Health Service and non-governmental organizations (NGO) will do the recruitment.

Eligible immigrants who accept to participate will sign the consent during routine visits at Diabetes clinics and will be randomized to the control or intervention group.

The intervention group will receive a co-created culture-tailored intervention of health promotion aimed to increase healthy diet, physical activity and compliance with treatment protocols for diabetes.

The control group will receive the health promotion activities routinely performed by Diabetes clinics at the recruiting centres.

The enrolment phase will last 4 months.

The intervention will last at least 3 months.

Follow-up visits will be performed 12 months after recruitment.

The study period will be between 01/01/2023 and 31/12/2025, compatibly with the trend of the COVID-19 emergency.

Questionnaires about diet and physical activity will be collected at baseline and 12-month visits, as well as anthropometric measures.

Blood and urine samples will be collected at baseline and at 12 months to measure glycated haemoglobin and other biomarkers.

[figure not shown]

Figure 1. DiabEthic study design.

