## **Interventions**

#### **Intervention A (addendum for operational protocol)**

The intervention will include key elements of proven efficacy for health promotion combined and adapted to each community through a co-design and co-creation process, involving service providers and end-users.

Stakeholders will include professionals involved in diabetes care and providing services to hard-to-reach populations, immigrants with diabetes (the final user), relevant people of the communities and professionals of the third sector. A combination of different methodologies (focus group, consultations, stakeholder meetings, and qualitative interviews among the others) will be used by each centre to co-create a community-tailored intervention [Leask CF 2019] adapted to the local context of each centre with a different implementation of key elements:

- a) Dietary habit: the key elements will be theoretical dissemination of information on healthy diet (i.e. cookbooks with healthy and easy-to-make recipes), and courses on healthy cooking targeted to family and factory cooks (i.e. how to cook healthy dishes respecting the preferences and the taste of the community of origin, but feasible with ingredients available in the hosting region).
- b) Physical activity: the key elements will be the promotion of organized physical activity compatible with the daily time restrictions of the patients, promotion of non-organized physical activity (i.e. analysing the possibilities of moving home-work on foot or by bicycle and using an opportunity map that shows parks and possibilities for spontaneous physical

activity), theoretical dissemination of information on adapted physical activity (i.e. lectures with sports instructors or healthcare professional with specific expertise). Use of apps to measure physical activity will be considered.

- c) Adherence to treatments: tools favouring compliance and glucose measuring, as well as culture-tailored information material on diabetes and its health implications will be used.

The intervention will last a minimum of 3 months and will include at least one individual counselling (IC), one family session, and at least two group sessions (FS) for dietary and physical activity courses. Mandatory elements for the intervention and a non-exhaustive list of optional elements, as well as, elements that can be modulated in the co-creation phase are reported by topic in Table 1.

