##### **Secondary endpoint**

Secondary endpoints include:

- Biomarkers related to lipid profile assessed through the collection of fasting blood samples: triglycerides (mmol/l), LDL (mmol/l), HDL (mmol/l), total Cholesterol (mmol/l), free fatty acids (mmol/l), anthropometric measures (height, weight, BMI, waist circumference) and health related behaviours.
- Anthropometric measures: weight, height and waist circumference, bioelectrical impedance analysis (BIA).
- Systolic and diastolic blood pressure.
- Physical activity and dietary habits self-reported data.
- Increase in adherence to Mediterranean Diet

- restriction of daily alcohol consumption (<160 kcal);
- compliance with WHO recommended exercise goals
- Indicators of compliance with individual therapeutic protocols in terms of number of attended visits, number of tests of renal function and glycaemic control, and drug prescription.

Blood and urine samples and anthropometric measures will be collected at baseline and 12-month follow up visits.

Physical activity and dietary habits data will be collected through a questionnaire on lifestyle, dietary habit and physical activity fulfilled by each participant during routine visits in Diabetes clinics. The questionnaires used to assess dietary habits will be the Mediterranean Diet Score, (MedDietScore).(Panagiotakos 2007) The questionnaire used to assess physical activity will be the International Physical Activity Questionnaire - Short Form, IPAQ-SF. (Mannocci 2010)

Therapeutic adherence will be assessed at baseline and follow up visits using the Diabetes Mellitus Treatment Adherence Scale (DMTAS). (Hou 2021)

Descriptive analysis of mean (or median) changes with relative SD (or IQR) and the proportion of patients reaching therapeutic/recommended targets will be used.

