## Study plan

### Study timeline (addendum for operational protocol)

The enrolment phase will last 4 months.

The intervention will last at least 3 months.

Questionnaires about diet and physical activity will be collected at baseline and 12-month visits, as well as anthropometric measures. The study timeline is reported in Figure 2.

Blood and urine samples will be collected at baseline and at 12 months to measure glycated haemoglobin and other biomarkers

[figure not shown]

Figure 2: Study timeline and data collection

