#### **Statistical plan**

Descriptive statistics will be calculated for baseline characteristics. The analysis will be intention-to-treat. Before/after variations of the glycated haemoglobin, lipid profile and renal function biomarkers, and anthropometric measure will be computed and standardized if opportune. Paired and unpaired tests will be used to assess the effects of the intervention and to analyse before/after within-group and between-group differences and changes in glycated haemoglobin. Changes in lifestyle habits (both related to diet and physical activities) will be described in terms of positive or negative changes.

Linear regression models will be used to analyse the variation of anthropometric measures and assessed biomarkers.

Multilevel linear models will be performed taking into account the influence of the centre on intervention efficacy.

We will perform a mediation analysis to understand which part of the changes in outcomes (glycated haemoglobin, lipid profile, and anthropometric measures) is attributable to changes in

physical activity, changes in diet, adherence to therapies, and other direct or unmeasured effects of the intervention.

The statistician will not be blinded to group assignments.

The statistical significance level will be set at 5%, and all analyses will be performed by using Stata 16 or SPSS 28.

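### The planned mediation analysis cannot support attributed shares for diet, physical activity or the adherence scale, because these are measured at the same two visits as the outcomes

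*Protocol*

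**What the plan says.** The Statistical plan of the protocol states: "We will perform a mediation analysis to understand which part of the changes in outcomes" is attributable to changes in "physical activity, changes in diet, adherence to therapies, and other direct or unmeasured effects of the intervention". The outcomes named are HbA1c, lipid profile and anthropometric measures.

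The measurement times are fixed elsewhere in the protocol:

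- **Diet, activity and anthropometry** (Study design, repeated in Study timeline): "Questionnaires about diet and physical activity will be collected at baseline and 12-month visits, as well as anthropometric measures".
- **HbA1c and other biomarkers** (Study timeline): "Blood and urine samples will be collected at baseline and at 12 months to measure glycated haemoglobin and other biomarkers".
- **Adherence scale** (Secondary endpoint, repeated in Data collection): "Therapeutic adherence will be assessed at baseline and follow up visits using the Diabetes Mellitus Treatment Adherence Scale (DMTAS").
- **Follow-up visits** (Study design): "Follow-up visits will be performed 12 months after recruitment".
- **Intervention length** (Intervention A): "The intervention will last a minimum of 3 months".

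The Secondary endpoint section also lists compliance indicators: "number of attended visits, number of tests of renal function and glycaemic control, and drug prescription". The section on adherence to intervention adds clinical records and attendance registers. The Blinding section says that neither participants nor investigators are masked. Diet and activity come from questionnaires that the participants complete.

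**The concern.** A mediated share rests on two steps: the arm changes the mediator, and the mediator changes the outcome. Randomisation supports the first step and the total effect. It does not support the second, because nobody is randomised to a level of diet or activity. That step needs, at the least, a mediator that precedes the outcome and no uncontrolled common cause.

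Here the change in diet, activity or DMTAS and the change in HbA1c, lipids or weight cover the same interval and end at the same visit. A patient whose HbA1c or weight has improved may report better habits because of that improvement. A patient who is generally more engaged may improve on both. Participants know their arm, so self-reports may also shift by arm. In addition, an intervention of minimum length that starts at recruitment ends about 12 − 3 = 9 months before the second questionnaire. A diet or activity change that came early and faded would then go unrecorded.

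What is at stake is the statement about mechanism: credit could go to diet, activity or reported adherence that the data do not establish.

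**Working it through.** The protocol gives no mediated share to reproduce, so the check has two parts: the timing, and what the planned analysis would return if a mediator had no effect.

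**1. Timing**

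| Quantity | Role | Times stated |
|---|---|---|
| Diet and activity questionnaires | mediator | baseline, 12 months |
| DMTAS | mediator | baseline, follow-up visits (12 months, per Study design) |
| HbA1c, other biomarkers | outcome | baseline, 12 months |
| Anthropometry | outcome | baseline, 12 months |
| Attended visits, tests, prescriptions, attendance registers | compliance indicators; use in the mediation model not stated | accrue during follow-up |

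For the first two rows, no measurement falls between baseline and the outcome visit.

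**2. Share credited to a mediator with no effect**

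Inputs from the Sample size section: difference 0.5 (read as HbA1c percentage points) and SD 1.3, used here as the SD of change. The standardised effect is 0.5 / 1.3 = 0.385. Assumed: the within-arm correlation *r* between reported behaviour and HbA1c improvement, arising only because improvement affects reporting.

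Let *A* be the arm, *Y* the HbA1c change and *M* the mediator change, both with within-arm variance 1.

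- *Y* = −0.385*A* + *e*
- *M* = −*rY* + *dA* + noise, with no path from *M* to *Y*; *d* is any extra reporting shift in the intervention arm
- Arm effect on *M*: *a* = 0.385*r* + *d*
- Coefficient of *M* in the regression of *Y* on *A* and *M*: *b* = −*r*
- Estimated share = *ab* / (−0.385) = *r*² + *dr* / 0.385

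Results, where the true share is 0% throughout:

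| *r* | *d* | Estimated share |
|---|---|---|
| 0 | 0 | 0% |
| 0.1 | 0 | 1% |
| 0.3 | 0 | 9% |
| 0.5 | 0 | 25% |
| 0.3 | 0.3 | 0.09 + 0.09 / 0.385 = 32% |

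The last row adds a second assumption, a 0.3 SD reporting shift by arm.

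**3. Whether the data could reveal the error**

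Three causal structures were simulated with 100 per arm and 4,000 runs each: mediator drives HbA1c, HbA1c drives mediator, and an unmeasured common cause. All were set to give the same joint distribution, with total effect −0.5, SD 1.3 and an assumed arm effect on the mediator of 0.4 SD. The expected share is 0.4 × 1.3 × *r* / 0.5 = 1.04*r*.

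| Within-arm correlation | Estimate: mediator drives HbA1c | Estimate: reverse direction | Estimate: common cause |
|---|---|---|---|
| −0.2 | 21% | 20% | 21% |
| −0.3 | 31% | 31% | 31% |
| −0.4 | 41% | 42% | 42% |
| −0.5 | 52% | 52% | 52% |

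In the first structure the true share is the expected figure; in the other two it is 0%. The central 95% of indirect-effect estimates excluded zero in every cell. At −0.2, for example, it ran from −0.223 to −0.018 for the first structure and from −0.225 to −0.019 for the reverse one. The estimate and its precision do not distinguish the structures.

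**4. Whether an interim questionnaire alone would help**

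Take the model of step 2, but read *M* at an interim time at which the arm effect on HbA1c is already present, and let *c* be the assumed correlation of interim with 12-month HbA1c. Then *b* = −*rc*, and the false share is *c* times that in step 2. At *c* = 0.5, 9% becomes 4.5% and 25% becomes 12.5%. At *c* = 0.9 they become 8.1% and 22.5%. A separate simulation with assumed coefficients and no mediator effect gave a mediator coefficient of about −0.24 without interim HbA1c in the model and about 0.00 with it.

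**The case against.** Several objections are fair.

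- **Adherence is not measured only at two visits.** A reader might infer that nothing is recorded while the intervention runs. The protocol does not support that: visits, tests, prescriptions and attendance accrue throughout, and the Statistical plan does not say which adherence measure it will use. The timing criticism therefore stops at diet, activity and DMTAS. The accrued counts do not rescue the rest: they do not measure diet or activity, and they can themselves respond to poor control.
- **A false share is not inevitable.** It needs a within-arm correlation; at *r* = 0.1 it is 1%, and at zero it is nil. The protocol gives no value, so the percentages show what could happen and not how likely it is.
- **Self-report is stated for diet and activity.** The mode of completing DMTAS is not stated, so arm-related reporting should not be assumed for it.
- **Mediation is not an aim or an endpoint.** A reader might infer that it will decide which components are carried to other communities. The benefit-risk section speaks only of the trial's results in general, and Intervention A combines diet, activity and adherence in one programme.
- **Assumptions and sensitivity analyses usually belong in the SAP.** This is true, and their absence here is not criticised. But the measurement schedule and the attribution are both in the protocol, and a SAP cannot supply a time point that was not collected. The category for other direct or unmeasured effects does not help either: it is what remains after the named shares, so it inherits their error.

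**Conclusion.** The point holds for diet, physical activity and DMTAS. With mediator and outcome changes taken over one common interval, the direction of effect is not identified, and an attributed share is not supported. Under assumed within-arm correlations of 0.3 to 0.5, with all of the correlation due to improvement affecting reports, a mediator with no effect would be credited with about 9% to 25% of the HbA1c effect. Only the effect 0.5 and SD 1.3 behind these figures come from the protocol. The conclusion itself needs only that reverse influence or a common cause is possible.

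The reading that DMTAS is taken at 12 months rests on the timing of follow-up visits in Study design. Figure 2, on the timeline, could not be read for this check.

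It would go too far to infer that the trial's efficacy result is in doubt. The randomised HbA1c comparison does not use the mediators. This is a minor point about a supporting analysis.

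**What to change.** In the Statistical plan, replace the attribution wording with an exploratory description of the association between concurrent changes in behaviour and changes in outcomes. State that no causal mediated share will be claimed for diet, activity or DMTAS.

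The cost is a weaker statement about mechanism. The change needs no new data and can be made even if data collection is complete.

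Repeating the questionnaires once between baseline and 12 months is not enough to keep the causal claim, as step 4 of the working shows. It would also need HbA1c at that same time point, in both arms, and the result would still assume no unmeasured common cause of mediator and outcome. Nor can such a visit be taken as already available at no extra cost: the pre-planned routine visits are described under Intervention B, for the control group, and no interval is given.

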#### **Study endpoints (addendum for operational protocol)**

##### **Primary endpoint**

The primary endpoint is the change in glycated haemoglobin (HbA1c; mmol/mol) between the recruitment and the 12-month follow-up visit assessed through the collection of fasting blood and urine samples.

The difference between groups of the mean change (and standard deviation) in glycated haemoglobin will be used to assess the effectiveness of the intervention.

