#### **Blinding (addendum for operational protocol)**

The randomization arm will not be masked to the participant nor to the investigator. The person who enrolls will be blinded to the random sequence until each patient will sign the informed consent (allocation concealment).

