##### **Data management**

Data will be entered with manual data entry on GDPR-compliant digital platforms as in use in the recruiting centres. The personal information will be stored locally and will be subject to technical

and organizational safeguards. For each participating subject, the system will generate a pseudo-anonymization code with the specification of the recruitment centre, as no individual can be identified without reference to personal information. This code will be present in each record relating to the same participant in the various tables of the CRF. Each centre will carry out quality controls of the data entered through crosschecks with the information present in the original sources (paper questionnaires, medical records).

Pseudo-anonymised datasets will be sent by each recruiting centre to the centre which will perform statistical analysis (Azienda USL-IRCCS di Reggio Emilia) according to the procedures reported in the Data Transfer Agreement at the end of the recruitment end follow-up.

The final analysis will be carried out when the 12-month follow-up will be available for all participants.

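### The Protocol rules out a blinded statistician without giving a reason, although the arm could be sent as a neutral code until the primary HbA1c analysis is locked

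*Protocol*

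**What the plan says.** The Protocol's Statistical plan makes a positive choice: "The statistician will not be blinded to group assignments". It gives no reason. The Blinding section opens the trial to two other roles, "The randomization arm will not be masked to the participant nor to the investigator", and says nothing about the analyst.

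On data flow, the Data management section says "Pseudo-anonymised datasets will be sent by each recruiting centre to the centre which will perform statistical analysis", and names the AUSL-IRCCS in Reggio Emilia as that centre. Study population lists the same institution among the four recruiting centres. Data management also plans a single final analysis once 12-month follow-up is available for everyone.

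On the primary analysis, the Primary endpoint section says "The primary endpoint is the change in glycated haemoglobin (HbA1c; mmol/mol) between the recruitment and the 12-month follow-up visit" and, for the comparison of the arms, "The difference between groups of the mean change (and standard deviation) in glycated haemoglobin will be used to assess the effectiveness of the intervention". The Statistical plan then offers several routes:

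- simple tests: "Paired and unpaired tests will be used to assess the effects of the intervention"
- regression: "Linear regression models will be used to analyse the variation of anthropometric measures and assessed biomarkers"
- a multilevel approach that allows for differences between centres

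None of these is called primary and no covariates are listed. Standardising the before/after changes is left to judgement.

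**The concern.** In an open-label trial with a laboratory endpoint, knowledge of the arm at the analysis stage does not bias how HbA1c is measured. It can bias what is done with the values afterwards. Someone has to decide whether to standardise, how to treat an odd value or a missing 12-month result, and which model carries the conclusion. If that person sees which group is the intervention, each decision can be made knowing whom it helps, even without intent.

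The sentence is not a detail awaiting a statistical analysis plan. A SAP written to follow this Protocol would inherit it. The analyst also works at an institution that recruits and delivers the intervention, which makes separation from the labels more useful and harder to achieve.

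**Working it through.** The plan gives no figure on this point, so most of the check sets sections side by side. A short calculation then shows what can and cannot be said about size.

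**1. Does anything need the labels before the final analysis?**

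| Possible need | What the Protocol says | Labels needed early? |
|---|---|---|
| Stopping rules | None (Premature study termination or suspension; IDMC section) | No |
| Reports to a monitoring committee | No committee will be created (IDMC section) | No |
| Monthly monitoring | Aggregated counts (Data collection) | No HbA1c by named arm |
| Final analysis | One, after all follow-up (Data management) | Only a coded arm |

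**2. Can the arm be hidden in the transferred data?** The HbA1c comparison needs the coded arm, centre, baseline and 12-month HbA1c, any baseline covariates, and a household identifier, since Intervention assignment keeps cohabitants in one arm. None of these names the arm. Fields that could reveal it are the attendance registers (Adherence to intervention) and the cultural mediation hours (Table 1: two hours per patient, mandatory in the intervention). They serve the adherence and mediation analyses and can be sent later.

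**3. How secure would the code be?** A pooled analysis needs the same A/B code at all four centres. Knowing the true arm of a single patient at any centre therefore breaks the code everywhere. Data retention keeps linkage keys at the recruiting centres, and the analysing centre is one of them. Coding works only if the analyst cannot reach the local allocation key.

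**4. What is left to choose?** The contrast is fixed as a difference in mean change. The test is not. Regression covers HbA1c, because Study design counts it among the biomarkers. Unpaired test, regression, multilevel model and standardisation all remain open in this document.

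**5. Can the effect of masking be expressed as a type I error rate?** For any of these two-arm comparisons, t = (mean change in one arm − mean change in the other) / SE. Swapping the labels turns t into −t, and the two-sided p = 2·P(T > |t|) does not change. Choosing the smallest two-sided p is thus equally possible with A/B labels, and masking alone changes its error rate by zero.

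A simulation of the null shows the size of that separate problem. The assumptions, which are not in the Protocol, were 200 patients, four centres of 50, baseline to 12-month correlation 0.3, 0.5 or 0.7, a modest centre effect, and 20,000 trials per setting. Centre entered as fixed effects, standing in for the multilevel model.

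| Rule | ρ = 0.3 | ρ = 0.5 | ρ = 0.7 |
|---|---|---|---|
| Smaller p of unpaired test and centre-adjusted analysis of change | 5.0% | 5.0% | 5.1% |
| Smallest p of four: the same two, each with and without baseline adjustment | 7.7% | 7.4% | 7.0% |

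The Monte Carlo standard error near 5% is √(0.05 × 0.95 / 20,000) = 0.15 percentage points, so the first row does not differ from 5%. The excess in the second row comes from baseline adjustment, which the Statistical plan neither names nor excludes.

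**The case against.** The strongest reply is that this is an openly disclosed design choice and not an error. The contrast is fixed, the analysis is by intention to treat, there is no interim look, and the endpoint is a laboratory value. Model choice, covariates and outlier rules commonly belong in a SAP, which is not available here and may settle them. All of this stands. It makes the point small, but it supplies no reason for the sentence.

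Several stronger readings are tempting, and the document does not support them:

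- A reader might infer that leaving the statistician unblinded raises the type I error to 7% or more. Step 5 shows that this figure reflects the lack of a named primary model plus an assumed baseline adjustment, and would be the same under A/B labels. Adding a comparison of 12-month values alone would not help the argument, because the Primary endpoint section specifies change.
- A reader might infer that the analyst is the only role that could be masked. The Blinding section unmasks participant and investigator only. HbA1c is measured by the clinical laboratories of the centres, whose staff might also be masked.
- A reader might infer that masking removes selective analysis at its source. It hides which arm a choice favours. It does not stop several models from being tried.

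It is also fair to object that masking could be imperfect where the analysing institution holds its own patients' allocations. That stands, and the fix has to address it.

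**Conclusion.** The point holds as a minor, inexpensive improvement. The Protocol excludes blinding of the statistician without a reason. Nothing in its monitoring or analysis schedule needs the labels early, and its own data transfer offers a ready step for coding the arm. With the test and standardisation open in this document, an unblinded analyst could make data-handling and model choices knowing which arm they favour.

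No numerical size can be attached. Sample size, power and alpha are unaffected, and the benefit depends on how much discretion the SAP leaves. The conclusion rests on two assumptions: that the sponsor has no unstated reason for early access to the labels, and that the analyst can be kept apart from the local allocation key. Masking supplements the naming of one primary model and does not replace it.

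**What to change.** Replace the sentence in Statistical plan with wording such as:

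> Each centre transfers the arm as a common neutral code (A/B). Attendance and intervention-only fields are sent later. The analyst has no access to the local allocation key, including at the analysing centre. One primary HbA1c analysis is run and locked before the code is broken. Mediation and adherence analyses follow.

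The primary HbA1c analysis should be named in advance, in the Protocol or the SAP, so that there is something definite to lock. If the sponsor has a reason for an unblinded statistician, it should be stated instead.

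The cost is small: one recoded variable per centre, a second file transfer, and an access restriction at the analysing centre. The remaining downside is that masking there may be imperfect. Patient care and the size of the trial do not change.
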